### Baseline Assessment and Randomization

After obtaining written informed consent, a baseline (pre-treatment) assessment will be performed. Subjects will be randomized into either the intervention or the control group. A study coordinator will randomize subjects by means of a computer-generated list of random numbers in blocks of six, stratified by gender. Treatment assignments will be concealed in consecutively-numbered sealed envelopes, which will be opened sequentially upon subject enrollment. As it is a single-blind study, the subjects and the study coordinator will not be blinded to the treatment assignment. However, the study coordinator will not take outcome measurements. All investigators and outcome assessors will be blinded to the treatment assignment.

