### Intervention Group

The PARO therapy will take place for 30 minutes once a week over a six week period, and will be delivered in a quiet room that is isolated from the common unit (ward) in the Occupational Therapy Department of Shatin Hospital, with minimal environmental distractions. The number of sessions, the length of each session, and the time frame of this study were decided based on the results of our pilot study (see Piloting of this section) and other PARO intervention studies which reported small or significant changes in mood, social interaction, and communication [15]. Given this, one 30-minute session per week for six consecutive weeks would allow sufficient time for identifying significant changes, and would also reduce the burden of commitment for subjects.

The PARO therapy will be delivered in a structured, small-group approach, in which a group of three to four subjects will be arranged to sit around a table with PARO in the centre. The subjects in each group can be substituted by subjects from other groups to optimize the chance of conducting each session. A facilitator who is familiar with the PARO caregiver’s manual will deliver the PARO therapy. Research team therapists will train the facilitator and monitor the sessions.

The PARO therapy is based upon a standardised framework, and involves activities around the concepts of engaging, social interaction, and communication. There are six stages/themes, including (1) introducing PARO, (2) baby-sitting PARO, (3) grooming PARO, (4) feeding PARO, (5) making over PARO, and (6) wardrobe PARO. During each session, the facilitator will show PARO to each subject and demonstrate how PARO responds. Subjects will be encouraged to touch and hold PARO, describe the features and appearance of PARO, and help take care of PARO. The session will proceed for at least 30 minutes. With one session per week, there will be at least a total of 180 minutes of the treatment in the six week period.

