### Outcome Measures

Measurement of outcomes will take place at pre-, during, and post-treatment. Mood, social interaction, and communication (ie, facial expressions and reactions towards each treatment) will be the primary outcome measures. Secondary outcome measures will include cognitive function and depressive symptoms, as well as caregiver burden. Pre-treatment and post-treatment assessments will be administered by a trained research assistant who will remain blinded to group allocation. Outcome measures administered at each time point are described in Table 1. Attendance at each session will be recorded for all subjects in the study.

**Table 1 table1:** Schedule of assessments.

Assessments	Screening	Pre-treatment	Treatment session number						Post-treatment
			1	2	3	4	5	6	
MMSE^a^	√ ^g^								√
CDR^b^	√								
CMAI^c^	√								
Demographics, lifestyle, and social characteristics		√							
Simplified face scale			√	√	√	√	√	√	
Observation table^d^			√	√	√	√	√	√	
CSDD^e^		√							√
ZBI^f^		√							√
Subjective impression questionnaire			√	√	√	√	√	√	
Qualitative comments from caregivers, facilitator, and therapists									√

^a^Mini-Mental State Examination (MMSE)

^b^Clinical Dementia Rating (CDR)

^c^Cohen-Mansfield Agitation Inventory (CMAI)

^d^Facial expressions and reactions towards each treatment

^e^Cornell Scale for Depression in Dementia (CSDD)

^f^Zarit burden interview (ZBI)

^g^The √ indicates at which point of the study the respective assessments will take place.

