#### Observation Table

In order to objectively examine changes in subjects’ social interaction and communication (ie, facial expressions, and reactions towards PARO or the psychosocial activities), treatment sessions will be videotaped and charted on an every-minute basis with an observation table by reviewing the videotaped clips after each treatment session. The observation table is a modified version of the one originally developed by Wada et al [24]. Responses will be classified into several categories, including expression, gaze, and interactions with PARO or the psychosocial activities, other subjects, facilitator, and therapists. The frequency of each response will be added, and depending on the duration of each session, the highest possible item-score is 30. The amount of time spent on verbal encouragement (prompting) offered will also be recorded.

To assess the inter-rater and intra-rater reliabilities of the modified observation table, a convenience sample of 11 community-dwelling older Chinese adults with mild cognitive impairment or mild to moderate dementia with a mean age of 80.5 (range 73-88 years, SD 4.9), of which 82% (9/11) were female, and with a mean MMSE score of 16.5 (range 9-24, SD 5.9) were recruited to receive a single 30-minute PARO therapy. The therapy sessions were videotaped and observed by two raters (one occupational therapist and one medical researcher) who independently marked the subjects’ facial expressions and reactions towards PARO on the modified observation table on an every-minute basis (with standardized rating criteria), on two different occasions with an interval of two to four weeks. Intraclass correlation coefficient (ICC) was used to measure the reliability of the ratings. The ICC of the inter-rater reliability was.95-1.00 and the ICC of the intra-rater reliability was.87-1.00 [43].

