### Study Strengths and Limitations

The proposed study has several notable methodological strengths. The use of videotaped observations will allow us to capture subjects’ facial expressions and reactions towards each treatment during the treatment sessions, of which standard questionnaires or proxy interviews may miss. The modified observation table assesses the degree to which people with dementia will respond with the treatment by videotaped observation, which has the advantage in that ratings were specifically developed in the context of social interaction and communication between elderly patients with dementia and PARO or the psychosocial activities and other subjects, the facilitator, and therapists. Inter-rater and intra-rater reliabilities of the table have been developed. Another strength of the proposal is the measurement of various variables including caregiver burden, and qualitative components from the caregivers, facilitator, and therapists, which could reflect mood and social behaviours in another perspective.

There are several limitations in the protocol. Although behavioural and psychological symptoms of dementia occur frequently in people with dementia, we will confine our study population to mild to moderate dementia, and will exclude those with behavioural and psychological symptoms of dementia, limiting the generalizability of the results to a wider population. It has been suggested that interventions for those with behavioural and psychological symptoms of dementia should tailor the person’s specific needs and capabilities [50]. As such, an individual-based setting may be more appropriate to those with behavioural and psychological symptoms of dementia, while a group-based setting is preferred to examine the use of PARO in stimulating social interaction and communication. Moreover, subjects will be recruited through clinical referrals from community day care centres, clinics, and day hospitals; they may not represent all older adults with dementia in the community. In addition, the simplified face scale, CSDD, ZBI, and the subject impression questionnaire are self-reported. Misreporting and non-reporting may occur.

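### The statement that all outcome assessors are blinded cannot hold for the video-coded primary outcome, and neither primary outcome has a blinded assessment

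*Protocol article*

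**What the plan says.** The primary outcomes are set out under Outcome Measures: "Mood, social interaction, and communication (ie, facial expressions and reactions towards each treatment) will be the primary outcome measures". Mood is measured with the simplified face scale. Social interaction and communication are measured with the observation table.

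On blinding, Baseline Assessment and Randomization says that "the subjects and the study coordinator will not be blinded to the treatment assignment", and then: "All investigators and outcome assessors will be blinded to the treatment assignment". Outcome Measures adds: "Pre-treatment and post-treatment assessments will be administered by a trained research assistant who will remain blinded to group allocation".

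On how the primary outcomes are obtained, the Observation Table section says that "treatment sessions will be videotaped and charted on an every-minute basis with an observation table by reviewing the videotaped clips after each treatment session". The face scale is taken before and after each session (Simplified Face Scale), and Study Strengths and Limitations states that "the simplified face scale, CSDD, ZBI, and the subject impression questionnaire are self-reported".

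On who is present at the sessions, Intervention Group says: "Research team therapists will train the facilitator and monitor the sessions".

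**The concern.** In a trial where subjects cannot be masked, the single-blind label rests on the assessors. The article claims that safeguard for every outcome assessor, but the way the video-coded primary outcome is collected rules it out.

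Coding of smiles, gaze and interaction is human judgement and can be influenced by what the rater expects of each arm. The article nevertheless presents the video coding as objective and counts it among the strengths. A reader, or someone grading risk of bias for a meta-analysis, who relied on the blinding sentence would rate detection bias as controlled for an outcome where it is not.

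**Working it through.** No arithmetic decides this point. The check sets the sections side by side.

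**1. Where each instrument is collected (Table 1) and who supplies the rating**

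| Instrument | Role | When | Rating made by | Blinded to arm? |
|---|---|---|---|---|
| Simplified face scale | primary | sessions 1–6 | the subject | no, as declared |
| Observation table | primary | sessions 1–6 | a rater watching session video | cannot be |
| CSDD | secondary | pre and post | research assistant, by interview with patient and caregiver | assistant: yes, as stated |
| ZBI | secondary | pre and post | research assistant administers; self-reported | assistant: yes, as stated |
| MMSE | secondary | screening and post | research assistant at post-treatment | assistant: yes, as stated |

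Count: primary instruments with a blinded assessment = 0 of 2. Primary instruments for which the blinding sentence is contradicted = 1 of 2, the observation table.

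**2. Can the observation table be scored blind?** Three statements bear on it.
- Intervention Group: subjects sit round a table with the robot in the middle.
- Control Group: subjects play table games.
- Observation Table: the response categories include interaction with the robot or with the psychosocial activities.

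A rater cannot record interaction with the robot without knowing that the robot is there. For those items masking is impossible. For expression and gaze it might be possible in principle, but the article describes none.

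**3. Does the blinded research assistant rescue the sentence?** Outcome Measures ties that person's blinding to the pre- and post-treatment assessments. Table 1 schedules neither primary instrument at those visits. The Abstract, however, says that a trained research assistant assesses subjects during treatment as well. If this is the same person, he or she would see the arm, and blinding of the post-treatment MMSE, CSDD and ZBI would also be in doubt. The article does not say whether it is the same person.

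**4. Does the sentence hold for all investigators?** Therapists described as belonging to the research team monitor the sessions and so know the arm. Whether they count as investigators is not stated.

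**5. Is the gap acknowledged?** Study Strengths and Limitations mentions misreporting and non-reporting of self-reports. It does not mention that the video coding is done with knowledge of the arm.

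**6. Do the reliability figures answer the concern?** The reported ICCs (.95–1.00 between raters, .87–1.00 within rater) come from 11 people who each received a single PARO session. They show that raters agree on PARO video. With no control sessions in the exercise, they cannot show that coding is even-handed between arms.

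**The case against.** Much can be said for the protocol, and several stronger readings fail.

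- **The blinding sentence is false for every primary outcome.** A reader might infer this, but it is not supported. The same section names subjects separately as unblinded, and the limitations list the face scale as self-reported. A declared-unblinded subject is not one of the assessors whom the sentence covers. The face scale therefore adds to the count of outcomes without blinded assessment, not to the contradiction.
- **The single-blind label is wrong.** Not so. The article explains what it means by the label and describes a blinded assistant for the pre- and post-treatment visits. With that scope the label is accurate.
- **The trial videos will be coded by someone involved in treatment.** One rater in the reliability exercise was an occupational therapist, but nothing says that this person will code trial video. The monitoring therapists are not described as outcome assessors either.
- **CSDD and ZBI rest on unblinded respondents.** This is stated for subjects. The caregivers' blinding status is not given.
- **The bias favours the robot.** This is plausible, but the document gives nothing from which to derive a direction or a size.

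It is also fair to say that arm-masking is infeasible for the interaction items, and that rater identity and clip handling are details an article may leave to the full protocol. Both stand. Neither removes the conflict, because the complaint is about a sentence that is stated and cannot be true, not about missing detail.

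**Conclusion.** The point holds in this form. The unqualified claim of assessor blinding contradicts the way the observation table is scored. The face scale is openly self-rated by unblinded subjects, so neither primary outcome has blinded assessment at any of the six sessions. The only blinded assessment described concerns secondary outcomes.

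The conclusion assumes that the session video reaches the rater unmasked and that the treatment-specific items are coded as described. The article gives no reason to think otherwise. It does not assume that the research assistant mentioned in the Abstract is the one named under Outcome Measures, or that the monitoring therapists are investigators; those are inconsistencies to resolve.

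The effect is on how far the primary results can be trusted and how they may be described. The sample size and the planned analyses are not affected.

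**What to change.** 1. **Baseline Assessment and Randomization:** limit the blinding sentence to the research assistant's assessments, namely CSDD and ZBI before and after treatment and MMSE after treatment (Table 1 places the earlier MMSE at screening). Then say that the observation table is coded with knowledge of the arm and that the face scale is self-rated by unblinded subjects.
2. **Abstract and Study Design:** keep the single-blind label, but only with that scope.
3. **Reconcile two pairs of passages:** the Abstract's research assistant who assesses during treatment with the blinded assistant under Outcome Measures, and the claim about all investigators with the research team therapists who monitor sessions.
4. **Observation Table:** qualify the statement that the coding is objective.
5. **Study Strengths and Limitations, and Conclusions:** list unblinded assessment of the primary outcomes as a limitation, and qualify the conclusions to match.

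The cost is wording and a less favourable blinding statement. Shuffling clips or masking session numbers is optional. It does not hide the arm, so it does not cure the fault, and coding clips from both arms in random order would have to be squared with the stated review after each session.

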### Intervention Group

The PARO therapy will take place for 30 minutes once a week over a six week period, and will be delivered in a quiet room that is isolated from the common unit (ward) in the Occupational Therapy Department of Shatin Hospital, with minimal environmental distractions. The number of sessions, the length of each session, and the time frame of this study were decided based on the results of our pilot study (see Piloting of this section) and other PARO intervention studies which reported small or significant changes in mood, social interaction, and communication [15]. Given this, one 30-minute session per week for six consecutive weeks would allow sufficient time for identifying significant changes, and would also reduce the burden of commitment for subjects.

The PARO therapy will be delivered in a structured, small-group approach, in which a group of three to four subjects will be arranged to sit around a table with PARO in the centre. The subjects in each group can be substituted by subjects from other groups to optimize the chance of conducting each session. A facilitator who is familiar with the PARO caregiver’s manual will deliver the PARO therapy. Research team therapists will train the facilitator and monitor the sessions.

The PARO therapy is based upon a standardised framework, and involves activities around the concepts of engaging, social interaction, and communication. There are six stages/themes, including (1) introducing PARO, (2) baby-sitting PARO, (3) grooming PARO, (4) feeding PARO, (5) making over PARO, and (6) wardrobe PARO. During each session, the facilitator will show PARO to each subject and demonstrate how PARO responds. Subjects will be encouraged to touch and hold PARO, describe the features and appearance of PARO, and help take care of PARO. The session will proceed for at least 30 minutes. With one session per week, there will be at least a total of 180 minutes of the treatment in the six week period.

### Control Group

Subjects assigned to the control group will be invited to practise a variety of psychosocial activities including a range of table games (eg, Chinese checkers, Jenga, board games etc). The activities will be held on exactly the same schedule as the intervention group (one 30-minute session per week for six weeks). All activities will be carried out in groups of three to four subjects, and will be facilitated by the same facilitator of the intervention group. The sessions will proceed for at least 30 minutes. With one session per week, there will be at least a total of 180 minutes of the treatment in the six week period.

### Outcome Measures

Measurement of outcomes will take place at pre-, during, and post-treatment. Mood, social interaction, and communication (ie, facial expressions and reactions towards each treatment) will be the primary outcome measures. Secondary outcome measures will include cognitive function and depressive symptoms, as well as caregiver burden. Pre-treatment and post-treatment assessments will be administered by a trained research assistant who will remain blinded to group allocation. Outcome measures administered at each time point are described in Table 1. Attendance at each session will be recorded for all subjects in the study.

**Table 1 table1:** Schedule of assessments.

Assessments	Screening	Pre-treatment	Treatment session number						Post-treatment
			1	2	3	4	5	6	
MMSE^a^	√ ^g^								√
CDR^b^	√								
CMAI^c^	√								
Demographics, lifestyle, and social characteristics		√							
Simplified face scale			√	√	√	√	√	√	
Observation table^d^			√	√	√	√	√	√	
CSDD^e^		√							√
ZBI^f^		√							√
Subjective impression questionnaire			√	√	√	√	√	√	
Qualitative comments from caregivers, facilitator, and therapists									√

^a^Mini-Mental State Examination (MMSE)

^b^Clinical Dementia Rating (CDR)

^c^Cohen-Mansfield Agitation Inventory (CMAI)

^d^Facial expressions and reactions towards each treatment

^e^Cornell Scale for Depression in Dementia (CSDD)

^f^Zarit burden interview (ZBI)

^g^The √ indicates at which point of the study the respective assessments will take place.

### Demographics, Lifestyle, and Social Characteristics

Demographic information such as age, gender, marital status, educational background, living status, lifestyle factors (eg, smoking and alcohol intake), social supporting network (eg, measures of participation in day care centre, cognitive/memory training, community activities, and supporting groups), attributes of the owners of pet (ie, animal preference, ever kept pets, and plan to keep pets) [41], and child care experiences will be extracted from pre-treatment questionnaires.

### Primary Outcomes

#### Simplified Face Scale

A simplified face scale will be used to assess mood state before and after each session. This very brief, pictorial scale of mood uses a sequence of 7 faces and does not require reading literacy [27]. The original face scale contains 20 drawings of a single face arranged in serial order by rows, with each face depicting a slightly different mood state [42]. However, sometimes the subjects were confused by the original face scale because it contained too many similar images. Thus, the scale was simplified by using only 7 images from the original set. The 7 faces range from very happy at the left to very sad at the right.

#### Observation Table

In order to objectively examine changes in subjects’ social interaction and communication (ie, facial expressions, and reactions towards PARO or the psychosocial activities), treatment sessions will be videotaped and charted on an every-minute basis with an observation table by reviewing the videotaped clips after each treatment session. The observation table is a modified version of the one originally developed by Wada et al [24]. Responses will be classified into several categories, including expression, gaze, and interactions with PARO or the psychosocial activities, other subjects, facilitator, and therapists. The frequency of each response will be added, and depending on the duration of each session, the highest possible item-score is 30. The amount of time spent on verbal encouragement (prompting) offered will also be recorded.

To assess the inter-rater and intra-rater reliabilities of the modified observation table, a convenience sample of 11 community-dwelling older Chinese adults with mild cognitive impairment or mild to moderate dementia with a mean age of 80.5 (range 73-88 years, SD 4.9), of which 82% (9/11) were female, and with a mean MMSE score of 16.5 (range 9-24, SD 5.9) were recruited to receive a single 30-minute PARO therapy. The therapy sessions were videotaped and observed by two raters (one occupational therapist and one medical researcher) who independently marked the subjects’ facial expressions and reactions towards PARO on the modified observation table on an every-minute basis (with standardized rating criteria), on two different occasions with an interval of two to four weeks. Intraclass correlation coefficient (ICC) was used to measure the reliability of the ratings. The ICC of the inter-rater reliability was.95-1.00 and the ICC of the intra-rater reliability was.87-1.00 [43].

